### Research aim and hypotheses

In order to evaluate the PATH-intervention, we compare families under treatment of trained pediatricians in the German state of Baden-Württemberg (IG) with those of a control group (CG; pediatricians not participating in the PATH-intervention) in the German state of Bavaria. More precisely, we put forward the following hypotheses: (1) Families with psychosocial burden who are under treatment of an IG-pediatrician use supportive services more often than burdened families treated by a CG-pediatrician (primary outcome). (2) As a precondition for successful referral to supportive services, we assume that pediatricians in the IG are better than their counterparts in the CG at (2a) identifying families with psychosocial burden, (2b) informing them about regional ECI services, and (2c) motivating them to use these services (proximal secondary outcomes). Thus, the proportion of families, who received information and were motivated, will be higher in the IG than in the CG. (3) From a socioeconomic point of view, the ratio between costs and effectiveness of the PATH-intervention will be positive (distal secondary outcome). (4) All involved stakeholders - the families with small children (0-3 years), pediatricians and members of the ECI network - appraise the PATH-intervention in a positive way (distal secondary outcome).

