### Study design and setting

This study is designed as a prospective quasi-experimental, controlled (matched-pair), longitudinal mixed-method trial [19]. It comprises a summative evaluation, as well as process evaluative study sections (Fig. 1). The summative evaluation is based on quantitative surveys. Participating families with small children (0-3 years) are asked to answer an online-survey at three measurement time-points: up to 7 days after a preventive medical check-up (U3-U7a) at the pediatrician (t1), follow-up at 6 weeks after the doctor’s visit (t2) and again 6 months later (t3). The pediatricians answer a questionnaire immediately after each medical check-up with a participating family. They will also answer a brief questionnaire on confounding factors (e.g. work experience) after the completion of the recruitment of families. Additionally, the evaluation is complemented by health economic analyses, including the analysis of health insurance data. As part of the process evaluation, we will conduct individual telephone interviews with participants of all stakeholder groups involved in the intervention – families, pediatricians and ECI network members. Another part of the qualitative process evaluation are video-assisted observations during the medical check-ups to examine treatment fidelity of the IG-pediatricians.

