### Procedure

#### Summative evaluation

##### Questionnaire survey

Participating families are asked to complete online-surveys including questions concerning sociodemographic information, psychosocial burden, the use of supportive services, as well as questions about information provision and motivation by the pediatrician. In addition, families are either asked to rate their satisfaction with a specific offer, or to state the reasons why they did not use it (see Table S1, Additional file 1, for the operationalization of psychosocial burden and Additional file 2 for the family questionnaire about supportive services). The survey takes place at three measurement time-points: up to 7 days after the medical check-up (t1), 6 weeks after the medical check-up (t2) and again at 6 months after the medical check-up (t3). The same person should answer all three surveys. At each time-point, participating families receive a link to the online-survey via e-mail. The link is valid for 7 days. The online-survey is available in four languages, namely German, Arabic, Italian and Turkish.

Immediately after a participating family leaves the medical check-up, the pediatrician rates in a short paper-pencil questionnaire whether the family is psychosocially stressed, and if so, the degree of psychosocial burden (Questionnaire for pediatricians, Additional file 3). Moreover, the pediatricians are asked whether they have addressed the perceived psychosocial burden with the family and to rate the family’s need for supportive services. At the end of the recruitment of families, the pediatricians answer a second paper-pencil questionnaire about possible confounding variables, such as the structural characteristics of the doctor’s office and work experience (Descriptive questionnaire for pediatricians, Additional file 4).

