### Study measurements and outcomes

Central for answering the research questions is to assess the risk factors and perceived psychosocial burden of the families. We therefore apply an additive index and count up the risk factors asked for, as is commonly used in research and previous studies [1, 20, 21]. The index comprises six domains, namely the (a) family background, (b) parent’s individual preconditions for dealing with care challenges, (c) parent’s psychological health, (d) difficulties during pregnancy and in interaction with the child, (e) special care challenges regarding the child, and (f) problematical caring behavior. Each domain consists of a set of questions asking for specific risk factors such as low educational qualifications, overcrowding, conflicting partnership, depression, early pregnancy or parental strains. In this context, we utilize commonly used instruments, e.g. the Patient Health Questionnaire (PHQ-4 [22, 23]) measuring parents’ depressive symptoms and the German Version of the Parenting Stress Index assessing challenges and the burden of being a parent [24]. In addition, we apply questions previously used in the representative study concerning the psychosocial burden of families with small children in Germany [25]. Table S1 (Additional file 1) shows the domains and assessed risk factors, and their operationalization with references to the applied, published instruments in detail. In the form of a patient-reported outcome, the participating families themselves answer the questions that underlie the assessment of these risk factors in the online-survey. In line with previous studies, which used the same risk factors as indicators for psychosocial burden [20], families meeting three or more risk factors are judged to have considerable psychosocial burdens (for the calculation of the additive index indicating psychosocial burden, please see Additional file 1).

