#### Secondary outcomes

Secondary outcomes are classified as proximal and distal outcomes. Proximal secondary outcomes are conceptualized as directly affected by the intervention and observable close to the intervention. In contrast, distal secondary outcomes are located more distant to the intervention and are likely influenced by other external factors than the intervention.

One secondary proximal outcome is the proportion of correctly identified families with psychosocial burden by the pediatricians. With one question, the pediatricians are directly asked whether they judge the family as burdened or not (yes-no question; Questionnaire for pediatricians, Additional file 3). Another two secondary proximal outcomes are, on the one hand, the information provision and, on the other, the motivation of the family with psychosocial burden by the pediatrician. To find this out, the list of the predefined supportive services in the family survey includes questions regarding these two aspects (Family questionnaire about supportive services, Additional file 2). Families, who have already stated to know about a specific supportive service, answer whether the pediatrician informed them about it and recommended them to use it.

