## Discussion

Representative studies showed that about 13% of the families with small children (aged 0 to 3 years) visiting a pediatrician for a preventive medical check-up have considerable risk factors [7, 5]. Such risk factors increase the probability for psychosocial burden in the family and the vulnerability to severe developmental consequences for the child, making early interventions urgently necessary. In this context, supportive services for burdened families can be beneficial. Although supportive services of the ECI are implemented nationwide, families with psychosocial burden rarely attend these services. The PATH-intervention therefore aims at training the pediatricians’ skills to facilitate the communication with burdened families with small children and the referral to tailored supportive services. Using a prospective quasi-experimental, controlled (matched-pair), longitudinal mixed-method design, we evaluate the target accuracy of this complex healthcare intervention. Quantitative data will allow us to evaluate the extent to which the intervention enables the pediatricians to identify and recommend supportive services to burdened families, and the families’ use of the supportive services of the ECI. Moreover, health-economic analysis will show the cost-effectiveness ratio of the PATH-intervention. Qualitative data will enable us to get a deeper insight into the subjective evaluation and acceptance of the PATH-intervention in the perspective of all the stakeholders involved, as well as in the pediatricians’ treatment fidelity in daily routine care.

By exploring the successful identification of burdened families, recommendation and usage of supportive services, this study could be a starting point for future research. Moreover, the results of this study could form the basis for the broader implementation of the PATH-intervention as standard care.

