Nevertheless, some limitations of the study should be mentioned. The evaluation is restricted to two structurally similar German states. Thus, the results may be influenced by specific characteristics of these two states, e.g. their relatively high economic performance. Furthermore, due to an initial briefing session to recall the intervention contents and the selective observations in the IG, as well as due to the study participation itself, it is unavoidable that the pediatricians are sensitized to the issue of families’ psychosocial burden. Therefore, it is possible that the pediatricians will act in a different manner to usual under study participation conditions.

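### As most naturally read, the outcome for hypothesis 2a measures sensitivity only, so more frequent flagging in the intervention group could pass for better identification

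*Protocol article*

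**What the plan says.** Under Research aim and hypotheses, the protocol article expects intervention-group (IG) pediatricians to do better than control-group (CG) pediatricians at "identifying families with psychosocial burden, (2b) informing them about regional ECI services", and at motivating families to use them. The first of these is hypothesis 2a. Its outcome, under Secondary outcomes, is worded: "One secondary proximal outcome is the proportion of correctly identified families with psychosocial burden by the pediatricians". The measurement is a single yes/no item: "the pediatricians are directly asked whether they judge the family as burdened or not". The reference is the family's own survey: "families meeting three or more risk factors are judged to have considerable psychosocial burdens" (Study measurements and outcomes).

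The rating is not confined to burdened families. Study design and setting says: "The pediatricians answer a questionnaire immediately after each medical check-up with a participating family". Questionnaire survey repeats that, once a participating family has left, "the pediatrician rates in a short paper-pencil questionnaire whether the family is psychosocially stressed".

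Data analysis treats secondary outcomes in the same way as the main analysis, a multilevel binary logistic model whose outcome is defined in burdened families. The cost-effectiveness section plans an ICER per correctly identified burdened family. Specificity, false positives, predictive value and agreement are not mentioned. The Background sets precise referral as the intervention's aim, and the Discussion says: "we evaluate the target accuracy of this complex healthcare intervention".

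**The concern.** A proportion computed only among burdened families rises whenever pediatricians say yes more often, whether or not they tell burdened from non-burdened families any better. If IG pediatricians lower their threshold, the 2a test could favour IG and be reported as better identification when what changed was the frequency of flagging. The identification ICER would credit the extra true positives and leave the extra false positives out of the effect count.

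The article gives reasons why a threshold shift is plausible. Its limitations paragraph concedes that "it is unavoidable that the pediatricians are sensitized to the issue" and names an initial briefing on the intervention contents and the observations in IG, along with study participation itself. Secondary outcomes also lists identification of burdened families among the reimbursed parts of the intervention. At stake are the conclusion on a named secondary hypothesis and one of the ICERs. The primary outcome is not affected.

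**Working it through.** **The article's sample size, for the family counts.** Inputs from Sample size considerations: 50% versus 10% use, power 0.80, alpha 5% (taken as two-sided; the article does not say), 15% burdened, 50% participation, 30% dropout, 40 pediatricians.

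- Per arm: n = [1.96·√(2·0.30·0.70) + 0.84·√(0.50·0.50 + 0.10·0.90)]² / 0.40² = 19.4, so 20 per arm and 40 in total.
- Families to ask: 40 / (0.15·0.50·0.70) = 762, or 19.05 per pediatrician. Rounded to 20 × 40 this is 800, as stated.

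The point does not depend on this figure, but it gives the t1 counts. 800 × 0.50 = 400 responders, or 200 per arm. Of these, 0.15 × 200 = 30 are burdened and 170 non-burdened per arm (60 and 340 overall). This assumes that the 30% dropout falls after t1.

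**Effect of a threshold shift.** The documents give no error rates, so those below are assumptions. PPV = 0.15·Se / (0.15·Se + 0.85·FP); accuracy = 0.15·Se + 0.85·(1 − FP).

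| | Se 50%, FP 10% | Se 70%, FP 30% |
|---|---|---|
| True positives of 30 | 15 | 21 |
| False positives of 170 | 17 | 51 |
| PPV | 15/32 = 47% | 21/72 = 29% |
| Accuracy | 0.075 + 0.765 = 84% | 0.105 + 0.595 = 70% |
| Youden (Se − FP) | 0.40 | 0.40 |
| Diagnostic odds ratio | 1 / (0.10/0.90) = 9.0 | (0.70/0.30) / (0.30/0.70) = 5.4 |
| d-prime | 0 + 1.28 = 1.28 | 0.52 + 0.52 = 1.05 |

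The 2a outcome gains 20 points. Of the 40 extra flags (72 − 32), 6 are true and 34 false. An ICER per correctly identified family counts the 6. Youden is unchanged, but the odds ratio and d-prime both fall, so by those measures discrimination worsens.

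**Holding discrimination exactly equal.** In an equal-variance signal-detection model, Se = 1 − Φ(Φ⁻¹(1 − FP) − d-prime). Power is for a two-sided comparison of sensitivity with 30 burdened families per arm, ignoring clustering.

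| d-prime | FP, CG to IG | Se, CG to IG | PPV, CG to IG | Power |
|---|---|---|---|---|
| 0 | 10% to 30% | 10% to 30% | 15% to 15% | 49% |
| 0 | 10% to 40% | 10% to 40% | 15% to 15% | 78% |
| 1 | 10% to 30% | 39% to 68% | 41% to 29% | 63% |
| 1 | 10% to 40% | 39% to 77% | 41% to 25% | 87% |

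A threshold shift alone can thus make the 2a comparison significant with no gain in discrimination. Smaller shifts would do so less often.

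**What the non-burdened families can show.** Ignoring clustering, detecting a false-positive rise from 10% to 21% with 80% power needs [1.96·√(2·0.155·0.845) + 0.84·√(0.09 + 0.1659)]² / 0.11² = 169 per arm, against 170 expected.

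**What the interaction can show.** At the first table's rates, the variance of the group × burden log odds ratio is 1/15 + 1/15 + 1/17 + 1/153 + 1/21 + 1/9 + 1/51 + 1/119 = 0.385, so SE = 0.62. Eighty percent power needs a ratio of odds ratios near exp(2.80 × 0.62) = 5.7. The term can also mislead: going from 50%/10% to 90%/30% raises the odds ratio from 9 to 9 / (0.30/0.70) = 21, although false positives triple.

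**The case against.** The strongest reply is that sensitivity suits the hypothesis. 2a is framed as a precondition for getting burdened families to services, the Background describes under-detection (pediatricians who wait and see, or who find burden hard to spot), and the primary outcome also concerns burdened families. Finding more of them is a real gain. That stands, and sensitivity should remain the 2a outcome. What does not follow is that higher sensitivity alone shows pediatricians to be better at identifying.

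The denominator is also inferred. The wording could be read as the share of flagged families who are burdened, a predictive value that over-flagging would lower. Sensitivity is the more natural reading given the burdened-family analysis, but the ambiguity is real and is a reason to write the denominator down. A statistical analysis plan that is not shown might add specificity, but the article itself already sets the outcome, its analysis and the ICER.

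A reader might go further and infer that trained pediatricians will over-flag. The documents do not support that. Part of the conceded sensitization comes from study participation, which both groups share, and nothing is said about thresholds or false positives. Nor should one infer that the ICER must look better: identification is a reimbursed cost component, so extra flags may raise costs too. Finally, the 340 non-burdened families are left out of this outcome, not necessarily out of the trial: the exploratory comparison of the number of services used is worded for families in general.

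**Conclusion.** The point holds in a limited form. On its most natural reading the 2a outcome is sensitivity alone, with no false-positive measure beside it, so it cannot separate better identification from more frequent flagging. This fits poorly with an article that speaks of precise referral and target accuracy. In the illustration the outcome rises 20 points while PPV falls from 47% to 29%. That rests on 15% prevalence from the article and on assumed error rates. A shift in IG is plausible but not shown. It would be wrong to say that the illustration leaves discrimination unchanged, since that is true of Youden's index only. This is worth changing because it alters what 2a and its ICER can conclude, at almost no cost. It does not touch the primary analysis.

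**What to change.** - **Define the outcome.** State that the 2a proportion is the share rated burdened by the pediatrician among t1 responders with three or more survey risk factors.
- **Add the other side.** Using all t1 responders with a pediatrician rating, estimate specificity (or the false-positive rate) and predictive values by group, with confidence intervals that account for clustering by pediatrician. One way is a mixed logistic model of the yes/no rating on group, burden and group × burden.
- **Fix the interpretation.** Read higher sensitivity in IG as better identification only together with the specificity estimate; otherwise describe it as more frequent flagging. Do not make the group × burden test an alternative success criterion, because it is imprecise and can favour IG when false positives have risen sharply.
- **ICER.** Report the false-positive rate by group beside the cost per correctly identified family.

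No new data are needed: pediatricians rate every participating family, and every family that completes the t1 burden items has a burden status. The cost is some extra analysis and wording. Precision will be modest. Ignoring clustering, 95% half-widths per arm are about 1.96·√(0.50·0.50/30) = 18 points for a sensitivity of 50% and 1.96·√(0.10·0.90/170) = 4.5 points for a false-positive rate of 10%. The joint result should therefore be reported as estimates with intervals.

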#### Treatment fidelity

To examine the realization of the PATH-intervention by the IG-pediatricians in their practice, we use video-assisted observations. A video camera is placed in the doctor’s room, thus filming the communication and interaction between the family and the pediatrician. The researcher is not present during the examination. Afterwards, the researcher on site asks the family if the doctor acted in some way different to usual. This short interview serves for detecting the influence of the research situation and the video camera on the doctor’s professional acting.

### Sample size considerations

#### Summative evaluation

In total, we intend to include *N* = 40 pediatricians in the study. In purpose of the planned statistical twins (matched pair approach), each group (IG, CG) should comprise *n* = 20 pediatricians.

Concerning the family sample, we calculated the sample size for the planned analyses (logistic regressions) of the primary outcome (proportion of burdened families making use of supportive services) using the software GPower. The underlying assumptions were a statistical power of 0.80 and a significance level of 5%. Concerning the effect size, we assumed that 50% of the families with psychosocial burden under treatment of IG-pediatricians would use supportive services, compared to only 10% of the burdened families of CG-pediatricians. Furthermore, we assumed that the portion of families with psychosocial burden will be about 15% in the overall sample. About 50% of the eligible families are presumed to participate in the online-survey, from which about 30% will drop out of the study up to the last follow-up measurement time-point. Thus, to detect a significant effect concerning the use of supportive services by families with psychosocial burden contrasting intervention to control group, a total of *N* = 800 families should be asked to participate by the pediatricians, namely *n* = 20 families per each pediatrician.

#### Process evaluation

We intend to interview *N* = 10 pediatricians of the IG and N = 10 ECI network members. Of the participating families, *N* = 20 families under treatment of IG-pediatricians should be interviewed. For these cases, we use purposeful sampling aiming at maximum variability regarding age and gender of the child, as well as concerning the reported psychosocial burdens in the first online-survey.

A similar purposeful sampling is used to select the sample for the observation study section. The observations are conducted with *N* = 14 families of IG-pediatricians. The families are selected based on the following criteria: the family, which is under treatment of the IG-pediatrician, attended the U3, U4 or U5 at the time of recruitment. In addition, the family reports considerable psychosocial burden in the first online-survey.

### Data analysis

#### Summative evaluation

Before hypotheses are tested, we will perform dropout analyses to ascertain the amount of missing values, the mechanism of missingness and imbalances between the groups regarding study dropout and missing values. As families are treated by pediatricians, their data is not independent. Consequently, we will calculate the design effect to examine whether multilevel models should be used [26] that appear appropriate. Hypothesis are thus examined by generalized linear mixed models, in which families’ belongingness to pediatricians are accounted for by a random effect (random intercept) on Level 2. Level 1 comprises the fixed effects, with which the hypotheses are tested. The primary hypothesis will thus be tested by a multilevel binary logistic regression analysis, in which the dependent primary outcome (use of supportive services by burdened families: yes / no) is predicted by the group-variable (IG or CG) as a fixed effect on Level 1. Additionally, propensity score adjustment [27] will be applied to control for imbalances between IG and CG regarding confounding variables of pediatricians and families. The following model represents the main analysis to test our primary hypothesis:$$\mathrm{Level}\;1:\mathrm{Outcome}=\beta_{0j}+\beta_1\ast\mathrm{group}+\beta_2\ast\mathrm{propensity}\;\mathrm{score}+r_{ij}$$$$\mathrm{Level}\ 2:{\beta}_{0j}={\gamma}_{00}+{\mathrm{u}}_{0j}$$

In sensitivity analyses (SA) we will perform the main analysis without propensity-score adjustment (first SA) and as complete cases analysis (second SA). In order to consider the time taken for families to use supportive services, we will perform a time-to-event analysis that predicts the cumulative incidence of the use of supportive services by families over the three measurement points (third SA). Furthermore, we will examine if families in the IG use more supportive services than families in the CG. This explorative analysis compares the number of supportive services used by families in the IG and CG. The hypothesis on secondary outcomes will be examined analogous to the main analysis, by means of multilevel binary logistic regression analyses with propensity score adjustment.

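### The plan poses the use of multilevel models as a question for an estimated design effect, yet fixes the random-intercept model as the main analysis; with 1.05 to 1.5 burdened families per pediatrician that estimate cannot justify dropping the pediatrician level

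*Protocol article*

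**What the plan says.** The Data analysis section (Summative evaluation) first accepts that families seen by the same pediatrician are not independent. It continues: "we will calculate the design effect to examine whether multilevel models should be used". The next sentence treats the matter as decided: "Hypothesis are thus examined by generalized linear mixed models", with pediatrician as a random intercept at Level 2. The primary hypothesis is assigned to a multilevel binary logistic regression. That model is written out as the main analysis, with a Level 2 error term for pediatrician. The secondary hypotheses are to be handled in the same way. No design-effect threshold is stated and no single-level model is offered.

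The Sample size considerations section (Summative evaluation) plans 20 pediatricians per group and 20 families approached by each, 800 in all. It assumes that "the portion of families with psychosocial burden will be about 15% in the overall sample", that about half of the families take part, and that about 30% of these drop out by the last follow-up. No ICC or design effect is listed among its inputs.

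**The concern.** If the mixed model is fixed, the design-effect check decides nothing and its stated purpose is misleading. If the check has force, the main analysis depends on the data. Both readings can be cited from the same paragraph.

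This matters because exposure to PATH is a property of the pediatrician: all families of one pediatrician are in the same group. Pediatrician-level variation therefore belongs in the standard error of every group comparison, whatever the sample estimate of clustering turns out to be. A pre-test with little ability to show clustering would tend to favour leaving that variation out. Hypothesis 2a is the most exposed, because its outcome is the pediatrician's own yes/no judgement of the family, so clustering by rater is to be expected.

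**Working it through.** **1. Reproducing the plan's figure.** Inputs from Sample size considerations: assumed service use among burdened families of 50% in the intervention group and 10% in the control group, and "a statistical power of 0.80 and a significance level of 5"%. Taking the test as two-sided (sidedness is not stated), without continuity correction:

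n per group = [1.96 × √(2 × 0.3 × 0.7) + 0.84 × √(0.5 × 0.5 + 0.1 × 0.9)]² / 0.4² ≈ 19.4, so 20 per group and 40 burdened families.

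Families to approach = 40 / (0.15 × 0.5 × 0.7) = 762, or 19.05 per pediatrician. Rounded up to 20 × 40 this is 800, the stated figure.

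**2. Burdened families per pediatrician.**
- At t1: 800 × 0.5 × 0.15 = 60, and 60 / 40 = 1.5.
- At the last follow-up: 60 × 0.7 = 42, and 42 / 40 = 1.05.

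If each pediatrician's count is Binomial(20, 0.075) at t1 and Binomial(20, 0.0525) at the last follow-up, about 18 and 11 of the 40 pediatricians respectively have two or more burdened families. Only these carry information on within-pediatrician similarity.

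**3. Possible size of the design effect.** DEFF = 1 + (m − 1) × ICC. Cluster sizes are very unequal, so the size-weighted mean is the better choice for m:
- Last follow-up: m = 1 + 19 × 0.0525 = 2.00
- t1: m = 1 + 19 × 0.075 = 2.43

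| ICC (assumed) | DEFF, last follow-up | DEFF, t1 |
|---|---|---|
| 0.1 | 1.10 | 1.14 |
| 0.2 | 1.20 | 1.28 to 1.29 |
| 0.3 | 1.29 to 1.30 | 1.42 to 1.43 |

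With the plain means of 1.05 and 1.5, DEFF could not exceed 1.05 and 1.5 even at ICC = 1. With the weighted means the limits are about 2.0 and 2.4.

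**4. How well the check can see clustering.** Simulation with 40 pediatricians, beta-binomial outcomes, an ANOVA estimate of the ICC and an outcome rate of 30%:

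| True ICC | Time | Estimated ICC ≤ 0 | 95% range of estimate | 5% F-test detects clustering |
|---|---|---|---|---|
| 0.10 | last follow-up | 36% | −0.47 to 0.67 | 10% |
| 0.10 | t1 | 31% | −0.28 to 0.49 | 13% |
| 0.20 | last follow-up | 24% | −0.39 to 0.76 | 19% |
| 0.20 | t1 | 17% | −0.20 to 0.60 | 28% |

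A cut-off of DEFF ≥ 2 is an assumption, since the article gives none. At a true ICC of 0.10 and a 30% rate it is met in under 1% of trials.

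**5. Type I error if a single-level test were used.** Simulation with no group effect, 20 v 20 pediatricians, a logit-normal random intercept and a pooled two-proportion z test. The ICC is on the latent logistic scale. Both the ICCs and the outcome rates for the null case are assumptions.

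| Outcome rate | Families | Rejection at latent ICC 0.1 to 0.3 |
|---|---|---|
| 30% | completers (about 42) | 5.7-5.9% to 7.4-7.6% |
| 50% (identification, 2a) | t1 (about 60) | 6.2-6.3% to 8.8-8.9% |
| 10% | completers | 4.2% to 5.1% |
| 10% | t1 | 5.2% to 6.5% |

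The ranges within a cell come from separate runs. For completers at the 30% rate, the z test already rejects in 5.5% of trials with no clustering, so part of the excess in that row is not due to clustering. With the ICC defined on the outcome scale (beta-binomial, 0.1 to 0.3, 30% rate), rejection is somewhat higher: 6.3 to 8.5% at the last follow-up and 6.8 to 10.2% at t1.

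**The case against.** The strongest reply is that the multilevel analysis is already committed. Directly after the design-effect clause, the text assigns all hypotheses to mixed models, writes the random intercept into the main equation and carries the approach over to the secondary outcomes. A reader might infer that the group tests will be run as if families were independent. The document does not support that: it contains no single-level test, no cut-off and no rule for dropping the pediatrician level. This part of the reply stands in full.

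Three further objections also stand:
- A reader might conclude that the design effect cannot exceed 1.05 or 1.5. That holds only for the unweighted mean cluster size.
- The 42 families are completers, while complete-case analysis is only the second sensitivity analysis, so the main analysis need not be limited to them. Without that restriction the count is at most the 60 at t1, and the check is weak there too.
- The simulated z test is not the planned test, and at the plan's own 10% control-group rate the inflation nearly disappears.

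It can also be said that handling of convergence failure is ordinary content of an analysis plan that is not shown. Its absence is accordingly not counted as a fault here. The fallback is suggested only because, with about one family per cluster, a zero variance estimate is a likely event, and it would reopen the same choice.

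What the reply does not remove is the wording itself. A check on whether to use a multilevel model has meaning only if the model could be dropped, and the article does not say that it cannot be.

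**Conclusion.** The point holds as an internal inconsistency of modest consequence. A data-dependent question about the model stands beside an unconditional main analysis, and on the article's own rates the data can hardly answer it. A low or negative estimated ICC would not be evidence that pediatrician clustering is absent.

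The risk is conditional on the check being acted on. In that case type I error would be about 6-9% instead of 5% for latent ICCs of 0.1-0.3 at outcome rates of 30-50%, most plausibly for hypothesis 2a. For the primary outcome at a 10% usage rate it would be about 4-6.5%, so little or no inflation. The counts rest on the article's recruitment assumptions. The ICC range, the 30% and 50% rates for the null case and the cut-off of 2 are assumptions of this review.

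**What to change.** In the Data analysis section:
- Remove the design effect as a basis for choosing the model, and report it descriptively with the estimated ICC.
- State that every IG-CG comparison, primary and secondary, accounts for pediatrician whatever the estimated ICC or design effect.
- State that if the random-intercept variance is estimated as zero or the model does not converge, inference stays at pediatrician level. Cluster-robust standard errors with a small-sample correction, or a permutation test over pediatricians, would serve; a single-level model would not.

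The cost is a few sentences and possibly slightly wider intervals. No new data are needed.
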